### Monitoring of adherence to the home-based HIIT protocol

During the intervention, all participants will be asked to wear an Actigraph wGT3X-BT accelerometer (Actigraph, LLC, Fort Walton Beach, FL, USA) for 7 days every 4 weeks as an objective measure of compliance to the intervention. The accelerometer data will be used to determine whether the total amount of time spent in vigorous intensity activity is different between the HIIT and CON. In addition, participants will be provided with an exercise diary and asked to log their exercise sessions as well as report on the rating of perceived exertion (a chart will be provided in the diary) for each session. Weekly mobile text messages will be sent to all participants including those in the control group, reminding them to maintain their compliance to the intervention. The Actigraph is a tri-axial accelerometer worn on the hip attached to an elasticated Velcro belt. The Actigraph will be provided to each participant for 1 week every 4 weeks during the intervention. Participants will be asked to wear the Actigraph around their waist for seven consecutive days of assessment for 24 h a day during the week of activity monitoring. Participants will be asked to only remove the Actigraph during showering, bathing or swimming activity. The time and duration that the Actigraph is removed for any reason will also need to be noted by the participant in their exercise diary.

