**Methods:**

One hundred and twenty women (18–40 years old) with a body mass index between 20 and 35 kg/m^2^, will be stratified according to their BMI (normal, BMI 20–24.9 kg/m^2^; or high BMI ≥25 kg/m^2^) and randomized into a HIIT exercising group (HIIT) or a non-exercising control group (CON). HIIT participants will perform exercises for 11 min/session six times per week for a period of 14 weeks. The 2 × 4 HIIT protocol will require a work phase of own-body weight exercise lasting 2 minutes (85% VO_2_peak), repeated four times and separated by a one-minute active rest phase (65% VO_2_peak). CON participants will be asked to maintain their normal habitual lifestyle. Outcomes of cardiorespiratory fitness, body composition, echocardiography, central blood pressure, arterial stiffness and biomarkers of cardiometabolic health will be measured before and after the 14-week intervention. Every 4 weeks during the intervention, an objective estimation of compliance to the study protocol will be assessed by measuring participant physical activity over 7 days using an Actigraph GT3X accelerometer.

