### Study design

This study will be a randomized controlled trial (Fig. 1), where equal numbers of participants (normal and high BMI) will be assigned to either a HIIT group (HIIT) or a control (CON) group. The study has been designed using the SPIRIT guidelines (Fig. 2 and Additional file 1). The reporting of the trial will be guided by the CONSORT statement for clinical trials. Women in the HIIT group will complete a home-based high intensity exercise program for 14 weeks. The control group will be asked to maintain their current activity and dietary behaviours. Physiological measurements of cardiorespiratory fitness, body composition and cardiometabolic health will be done at baseline and on completion of the intervention at the 14th week. Habitual activity behaviours will be determined objectively using accelerometers for a week prior to the start of the intervention and for a week following the intervention. During the intervention, monitoring of and adherence to the HIIT protocol will also be assessed with accelerometers and an exercise diary. The study has been approved by the University of the Witwatersrand Human Research Ethics Committee (protocol number: M180253). Informed consent will be obtained from all participants prior to entry into the study. The trial has been registered on the Pan African Clinical Trial Registry (www.pactr.org - id no: PACTR201806003434299).

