### Study participants/eligibility criteria

Women between the ages of 18 and 40 years will be invited to participate in the study. Women will be included if they have a BMI between 20 and 35 kg/m^2^ (normal to obese BMI categories) and are free from injury and/or known clinical conditions which would exclude them from partaking in exercise as assessed using the physical activity readiness questionnaire (PAR-Q). Known clinical conditions include family history of sudden death, uncontrolled hypertension, type I or type II diabetes and cardiovascular disease. No pre-requisite training background is required however participants will be excluded from the study if they report engaging in competitive exercise or take part in a structured exercise programme that has been prescribed by a physical trainer or other health-related exercise professional. Exclusion criteria are also women with a BMI < 20 kg/m^2^ or > 35 kg/m^2^, and if they report any diagnosed underlying cardiometabolic condition including hypertension, diabetes or cardiovascular disease. All volunteers will be informed verbally and in writing of the procedures of the study before signing an informed consent form and completing screening questionnaires. Participants will be asked to maintain their habitual diet throughout the study.

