### Outcome measures

The primary outcome of the trial is a change in cardiorespiratory fitness after the 14-week HIIT intervention. Secondary outcomes are changes in body composition, cardiovascular health and metabolic biomarkers of health, as well as measures of feasibility and physical activity and sedentary behaviour levels. Both primary and secondary outcomes will be measured before and after the 14-week intervention (Fig. 2).

Table 1 summarises the outcome measures to be made and the time points at which they will be measured during the study.

**Table 1 Tab1:** Indication of physiological variables measured and timepoints of each measurement

Variable	Timepoints measured
*Primary outcome*	
Peak VO_2_, HR at peak VO_2_, HR at 65 and 85% peak VO_2_	Baseline, post-intervention
*Secondary outcomes*	
Anthropometry	
Skinfolds	Baseline, post-intervention
Body mass and waist:hip	Baseline, every 4 weeks during intervention, post-intervention
Brachial blood pressure	Baseline, post-intervention
Central blood pressure and arterial stiffness	Baseline, post-intervention
Echocardiography	Baseline, post-intervention
Biomarkers of metabolic and cardiovascular health	Baseline, post-intervention
Feasibility (adherence and dropout rate)	Baseline, every 4 weeks during intervention, post-intervention
Accelerometry	Baseline, every 4 weeks during intervention, post-intervention

*VO*_*2*_*peak* Peak oxygen consumption, *HR* Heart rate

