### Study procedures

#### Study visits

Volunteers will be required to visit the laboratory for an information session on the study. Eligible participants will then visit the laboratory to have their baseline and post-intervention measures taken. Participants in the exercising group will perform the HIIT program for 14 weeks in their own homes. During the intervention all participants will also visit the laboratory every 4 weeks (4th, 8th, and 12th weeks) to have an accelerometer fitted for measures of seven-day habitual activity. At these visits, body mass and waist-hip ratio will also be measured. Participants will be asked to refrain from consuming alcohol or caffeine for at least 24 h and food for at least 8 hours (eight-hour fast) before visiting the laboratory. Participants will also be asked to refrain from performing strenuous exercise 48 h prior to their measurement days. Post-intervention measurements will be performed a minimum of 48 h and a maximum of 4 days after the end of the HIIT intervention.

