### Control group

The CON participants will undergo the maximal exertion treadmill test but will not perform the HIIT exercises over the 14-weeks. Instead they will be asked to maintain their habitual activity and dietary habits at the time of recruitment and to not start any new exercise regimen during the 14 weeks. However, at the end of the 14-week follow up, participants will have the chance to receive the list of the HIIT exercises including their training intensities (from the maximal exertion test) and training frequencies to perform at their leisure. The research assistant will demonstrate the exercises to them.

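### The only stated use of the accelerometer as a compliance measure is a between-arm difference in vigorous time, which by itself does not separate HIIT non-adherence from exercise uptake by controls

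*Protocol article*

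**What the plan says.** In the protocol article, the section on monitoring of adherence has every participant wear the device "for 7 days every 4 weeks as an objective measure of compliance to the intervention". The one use it then gives for these data is to "determine whether the total amount of time spent in vigorous intensity activity is different between the HIIT and CON". The Abstract describes the same role: "an objective estimation of compliance to the study protocol will be assessed by measuring participant physical activity over 7 days".

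Other sections bear on how that contrast can be read:

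- **When the device is worn.** Study design: "Habitual activity behaviours will be determined objectively using accelerometers for a week prior to the start of the intervention and for a week following" it. Study visits: "all participants will also visit the laboratory every 4 weeks (4th, 8th, and 12th weeks) to have an accelerometer fitted". Table 1 lists the same time points.
- **Activity as an outcome.** The secondary outcomes under Outcome measures include activity itself: "as well as measures of feasibility and physical activity and sedentary behaviour levels".
- **Diaries.** Participants log their sessions and perceived exertion. The Feasibility section takes the count of completed sessions, and the number of women not reaching the intended exertion, from these diaries.
- **Who may enter.** Eligibility criteria: "No pre-requisite training background is required". The exclusion covers competitive exercise and programmes prescribed by a professional.
- **Controls.** They are asked to keep their usual activity and diet and "to not start any new exercise regimen during the 14 weeks". Weekly reminder messages about compliance go to both arms.

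**The concern.** Compliance with HIIT is a property of the women assigned to HIIT. A difference between arms in total vigorous time depends on what both arms do. It shrinks when HIIT women skip sessions, and it shrinks equally when controls become more active. It also shrinks when HIIT women do their sessions but give up vigorous exercise they used to do. That is possible here, because women who exercise on their own initiative are eligible and the request to keep usual activity is stated only for controls. Women who leave the study are absent from later wear weeks, so the contrast gradually comes to describe those who remain.

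This matters because adherence is part of the feasibility aim, and the Discussion names compliance as a likely limitation. The Background reports that 23% of participants were fully adherent in the one earlier home-based HIIT study it identifies. Heart-rate monitors are not supplied for home sessions and the diary is self-report, so the accelerometer is the only objective check. If VO2peak changes little, the reader will want to know whether sessions were not done, were done but matched by activity among controls, or were done without benefit. The one stated contrast does not answer that.

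**Working it through.** **The protocol's own figures.** From the section on the home-based intervention, a session has four 2-minute work phases with 1-minute rests between them: 4 x 2 + 3 x 1 = 11 min. Six sessions give 6 x 11 = 66 min/week, which matches the stated total. Work phases alone are 4 x 2 x 6 = **48 min/week**. Table 2 shows longer rests but the same four 2-minute work phases, so 48 does not depend on that difference. The protocol states no expected size for the vigorous-time contrast.

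**Assumptions.** Work phases register as vigorous and rest phases do not. Both arms have the same mean baseline vigorous time, b min/week (no value is given, so b = 0, 20 and 60 were tried). Controls who take up exercise add 48 min/week. There is no other drift in activity.

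**Scenario A: a share p of HIIT women stop and controls do not change.**
HIIT mean = b + 48(1 - p); CON mean = b; difference = 48(1 - p).

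**Scenario B: all HIIT women comply and a share p of controls take up exercise.**
HIIT mean = b + 48; CON mean = b + 48p; difference = 48(1 - p).

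The baseline cancels, so the two differences are equal for every p and every b:

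| p | Difference, A | Difference, B | Change from baseline, A (HIIT / CON) | Change from baseline, B (HIIT / CON) |
|---|---|---|---|---|
| 0.25 | 36 | 36 | +36 / 0 | +48 / +12 |
| 0.50 | 24 | 24 | +24 / 0 | +48 / +24 |
| 0.75 | 12 | 12 | +12 / 0 | +48 / +36 |

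All entries are min/week. The last two columns are the same for b = 0, 20 and 60. Arm-specific change therefore separates A from B, and the single difference does not.

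**Why the baseline week is needed.** Arm means without it can still be ambiguous. Under B with b = 20 and p = 0.5, the means are 68 and 44. Under A with b = 44 and p = 0.5, they are 44 + 24 = 68 and 44, the same pair. The baseline week shows which applies.

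**Scenario C: substitution.** If each HIIT woman does every session but drops s minutes of usual vigorous exercise, her change from baseline is 48 - s. With controls unchanged, the between-arm difference is also 48 - s. At s = 48 both are 0 although every session was done. This extreme needs at least 48 vigorous min/week beforehand in each HIIT woman, a figure the protocol neither gives nor rules out. Change from baseline alone does not resolve this case, so a second check against logged sessions is needed.

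**Coverage.** The three wear weeks during the intervention cover 3 x 7 = 21 of 14 x 7 = 98 days, about 21%.

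**The case against.** The strongest reply is that the ambiguity arises only if two arms are collapsed into one number. Comparing the arms requires both means, and the device is worn in both arms at baseline, three times during the intervention and afterwards. Physical activity is a listed secondary outcome. The Statistical analysis section plans a mixed model with group and time as fixed factors and baseline activity as a covariate, and says secondary outcomes in the four groups will be handled similarly. An analysis by group and time would show which arm moved. The diary already counts sessions per woman. A journal article may also leave compliance rules and weekly denominators to a fuller document.

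Much of this stands. A reader might infer that the trial cannot distinguish women who stopped from controls who started, or that adherence goes unmeasured. The documents do not support either reading: the data exist, and a self-reported adherence measure is planned and will be reported. Nor is the primary VO2peak comparison affected. A rule counting controls as switchers at 48 min/week or more would also be arbitrary, since it would pass over a control who added 40.

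Three things remain. The article does not leave the use of the accelerometer for compliance open; it states one use, and that use does not measure compliance with HIIT. The model section does not name accelerometry, and a baseline-adjusted between-arm difference would still be 24 in both scenarios at p = 0.5. The diary is self-report, so it does not supply the objective check that the accelerometer is meant to provide.

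**Conclusion.** The point holds as a weakness in the stated analysis. The single between-arm contrast equals 48(1 - p) min/week under either explanation, for example 24 when half the HIIT women stop or half the controls take up equal exercise, and it is not a count of HIIT sessions done. This rests on equal baselines, work phases that register as vigorous and equal uptake in controls. The documents give no expected vigorous time or standard deviation, so the power of the contrast cannot be assessed. Data collection is adequate for arm-specific analysis. The consequence is limited to the feasibility conclusion and to the explanation of a small VO2peak effect, but for both of these a better analysis is available at low cost and should be specified.

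**What to change.** State in the plan that:

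1. The accelerometer measure is each woman's change in vigorous minutes from her own baseline week at weeks 4, 8 and 12. Report it separately by arm, as adherence in HIIT and uptake in CON, with the number of women contributing at each week.
2. In HIIT, sessions logged in the diary during wear weeks are cross-checked against vigorous bouts recorded in the same week or on the same day, using start time only where it is available. This is needed because change from baseline cannot reveal substitution.
3. Uptake in CON is shown as a distribution of changes, without a cut-off.
4. The between-arm difference in vigorous time is kept as description.

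The cost is a little more analysis of data already collected. Recruitment and data collection are under way, so start times cannot be recovered for diaries already completed without them; matching by day or week avoids relying on them. The match rate is a lower bound, because a hip-worn device may miss some own-body-weight movements, and it speaks only for the wear weeks.

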### Data collection

#### Cardiorespiratory fitness

Measures of peak and submaximal relative oxygen consumption and heart rate will be determined as measures of cardiorespiratory fitness. These data will be collected using the maximal treadmill test described earlier, before the start of and at the end of the 14-week intervention.

#### Feasibility

Completion, dropout rates and intervention adherence will be used to determine the feasibility of the low-volume home-based HIIT intervention [57]. Feasibility will be reported using the following 1) the number of drop-outs after the intervention as a proportion of the number of recruited participants, 2) the number of HIIT sessions completed over the 14-week intervention period and 3) the number of participants who report not achieving the desired exertion level during the HIIT sessions at home. Data for points 2 and 3 will be collected using the exercise diaries.

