## Methods/design

### Study objectives

This randomised controlled trial will compare the effects of a 14-week low-volume high-intensity interval training intervention on cardiorespiratory fitness, body composition and cardiometabolic health in women of normal body mass and women with overweight/obesity. In addition, adherence to and drop-out rate of the intervention will be measured to determine feasibility. We hypothesise that at the end of the 14-week intervention, women with overweight/obesity performing HIIT will have significant changes in their cardiorespiratory fitness and cardiometabolic health regardless of a change in body composition. We also expect that a low-volume HIIT intervention will be feasible in this cohort of women.

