#### Sample size determination

Based on a small effect size of 0.20 (Cohen’s f) for an improvement in relative VO_2_peak after HIIT versus no HIIT [42], performing a priori sample size calculation for a repeated measures analysis of variance with an expected correlation of 0.50 between measurements, alpha of 0.05 and 85% power of detection, a total sample size of 60 women will be required (G*Power, version 3.1.9.2). The sample size will be doubled to account for further planned analysis of secondary outcomes in sub-groups of normal and high BMI women (HIIT normal BMI, HIIT high BMI, CON normal BMI, CON high BMI). The target sample size will be therefore be 120 women exclusive of drop outs.

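### The feasibility drop-out rate is defined over all recruited women, about half of them planned controls, so it does not measure drop-out from the HIIT programme

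*Protocol article*

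**What the plan says.** The Feasibility section states its purpose first: "Completion, dropout rates and intervention adherence will be used to determine the feasibility of the low-volume home-based HIIT intervention". It then lists three reported measures. The first is "the number of drop-outs after the intervention as a proportion of the number of recruited participants", and no arm is named. The other two are the count of HIIT sessions completed and the count of women who report not reaching the intended exertion. For these, "Data for points 2 and 3 will be collected using the exercise diaries".

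The Study objectives describe the target differently: "adherence to and drop-out rate of the intervention will be measured to determine feasibility". They also state an expected result: "We also expect that a low-volume HIIT intervention will be feasible in this cohort of women".

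Two other sections fix the denominator. Study design plans that "equal numbers of participants (normal and high BMI) will be assigned to either a HIIT group (HIIT) or a control (CON) group". Sample size determination says "The target sample size will be therefore be 120 women exclusive of drop outs" and gives no expected drop-out rate. According to the Control group section, control women take the treadmill test and keep their usual habits. They are offered the exercises only after follow-up.

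**The concern.** A woman can drop out of the HIIT programme only if she was assigned to it. A control woman who leaves the trial says something about retention in the study, but nothing about whether six home sessions a week can be sustained. A denominator of all recruited women mixes the two.

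The word recruited does not plainly mean the HIIT arm. Under Statistical analysis, characteristics are to be reported for everyone recruited into the study, and the Recruitment section uses the word for the whole trial, before allocation.

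Feasibility is a stated aim with a stated expectation of success, and the drop-out rate is one of only three measures used to judge it. If the definition is followed as written, the figure quoted for the programme can be too low or too high, depending on which arm loses more women. A reader who has only that figure cannot tell which.

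**Working it through.** **The plan's own figures.** The protocol gives no drop-out rate, so there is none to reproduce. Its total of 60 for the primary outcome does reproduce. A two-group, two-measurement interaction test with f = 0.20, correlation 0.50 and alpha 0.05 has power 0.861 at N = 60, against the 85% required. That calculation does not depend on how drop-out is defined.

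**Inputs.**
- Target of 120 women, 60 HIIT and 60 CON (Sample size determination; Study design; Randomisation).
- Drop-out rates dH (HIIT) and dC (CON). These are assumptions, because the protocol states neither.

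**Formula.** The declared statistic is

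pooled = (60·dH + 60·dC) / 120 = (dH + dC) / 2.

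It falls short of the HIIT rate by

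dH − (dH + dC)/2 = (dH − dC)/2.

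**Results over a range of assumed rates.**

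| HIIT rate | CON rate | Reported (pooled) | Error for HIIT |
|---|---|---|---|
| 20% | 10% | 15% | 5 points too low |
| 30% | 10% | 20% | 10 points too low |
| 40% | 10% | 25% | 15 points too low |
| 50% | 10% | 30% | 20 points too low |
| 20% | 20% | 20% | none |
| 10% | 20% | 15% | 5 points too high |

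**Precision.** Take the 30%/10% row. HIIT drop-out is 0.30 × 60 = 18 of 60, with a Wilson 95% interval of about 20% to 43%. The pooled count is 18 + 6 = 24 of 120, with a Wilson interval of about 14% to 28%. The pooled interval is narrower, but it excludes the assumed HIIT rate of 30%. Its extra precision belongs to a different quantity.

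**Allocation.** Equal arms are the plan. The Randomisation section draws each assignment independently with a spreadsheet function, which does not guarantee an exact half. If a fraction w of the women are in HIIT, the error is (1 − w)(dH − dC), which equals (dH − dC)/2 at w = 1/2. A modest imbalance therefore changes the size a little and leaves the direction as it was.

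**The case against.** The strongest reply is that the pooled reading is not the only one. The lead sentence of the section concerns the HIIT intervention, the other two measures can apply only to HIIT women, and the Study objectives speak of drop-out from the intervention. The protocol also commits to CONSORT reporting, which shows losses by arm, and nowhere says that drop-out will be reported only in pooled form. A reader could then work out the HIIT rate.

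This shows that the intended measure was probably arm-specific and that the losses need not be hidden. It does not alter the statistic that the section declares. That statistic still conflicts with the objectives, and it is the one that would be quoted as the feasibility result.

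It is also fair to object that the direction of error is unknown. Dilution of HIIT drop-out is plausible given the demands of the programme. But control women receive no exercise programme during the trial and might leave more often. The 23% full adherence cited in the Background comes from a 12-month study of another programme, and it is not a drop-out rate.

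A reader might go further and infer from the diary sentence that adherence rests on diaries alone and will be overstated. The documents do not support this. Study design says that "adherence to the HIIT protocol will also be assessed with accelerometers and an exercise diary", and the section on monitoring of adherence plans accelerometry in all participants, for 7 days every 4 weeks, as an objective compliance measure. Accelerometry is not among the three listed feasibility measures, but that does not make diaries the trial's only source. Nor does the protocol confine the session count to returned diaries or say how unreturned ones are handled. No bias in adherence can be computed from it.

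**Conclusion.** The point holds for the drop-out denominator only. The protocol judges the HIIT programme by a rate whose denominator, as written, includes the control arm, and this does not match the quantity named in its own objectives. At equal allocation the error is half the difference between the arms' rates. Under the assumed rates above, that runs from 20 points too low, through zero, to 5 points too high. The direction is conditional on which arm loses more women, and the protocol gives no basis for fixing it. No claim about overstated adherence is made.

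The consequence is limited to a secondary aim. The protocol sets no feasibility threshold that the figure would trip, and the primary outcome and its sample size do not depend on it. The correction is still worth making, because the definition is explicit, feasibility is a headline aim, and the repair is simple.

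**What to change.** In the Feasibility section, replace the first measure with: women in the HIIT arm who drop out, divided by women randomised to HIIT, with a 95% confidence interval and the corresponding control-arm rate alongside. This brings the section into line with the Study objectives. A pooled rate may still be given, provided it is labelled as retention in the trial as a whole.

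The cost is wording only. Allocation is recorded for every woman and drop-out is already collected, so no new data are needed. There are two downsides. The reported figure may look less favourable than the pooled one, and an estimate from about 60 women is less precise than one from about 120. In the 30%/10% example the interval is about 23 points wide (20% to 43%) rather than about 14 (14% to 28%).
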